In TKA, the extent of surgical trauma significantly influences postoperative pain and recovery. Plasma CRP, a well-established biomarker of tissue injury and inflammation, is commonly used to monitor recovery due to its rapid response, high specificity for acute inflammation, and ease of measurement, especially in elderly arthroplasty patients. CRP was selected as the primary outcome because of its association with osteoarthritis severity, surgical response, and postoperative complications, typically peaking on the third postoperative day [17].

Blood samples will be collected in an outpatient setting at four periods: before and after the eight-week prehabilitation program and three and 30 days post-TKA in both the experimental and control groups. The preoperative measurement one day before surgery (t3 in Figure 1) was timed to reflect chronic systemic adaptations resulting from prehabilitation while minimizing the confounding influence of acute exercise responses. This decision is supported by evidence showing that CRP typically returns to baseline (or a new post-exercise baseline) within six days after cessation of exercise [18]. The third postoperative day (t5) was selected to capture the peak inflammatory response following surgery, as supported by TKA-specific literature [17]. This time point also coincides with the typical hospitalization period, facilitating consistent, in-hospital sample collection. In the long term, given the anti-inflammatory effects of physical exercise, sustained reductions in CRP levels may reflect the effectiveness of the intervention in modulating systemic inflammation and promoting recovery [14].

Given that CRP levels can be influenced by factors such as sleep deprivation and acute infections, additional control measures will be implemented. Participants will report their average sleep duration and quality during the week preceding each blood draw (except for the third-day post-TKA measurement), as insufficient or disturbed sleep is associated with elevated CRP levels. Additionally, clinical symptoms suggestive of viral or bacterial infections (e.g., fever, sore throat, cough, or malaise) will be assessed before each collection since such conditions may increase CRP levels and confound the interpretation of the intervention's effects [19]. These precautions aimed to strengthen the internal validity of CRP as a primary outcome by minimizing interference from unrelated acute inflammatory processes.

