Additional blood biomarkers

Beyond CRP, additional biomarkers will be assessed simultaneously to strengthen inflammatory indicators and provide insights into tissue regeneration, nutritional status, and thromboembolic risks associated with TKA and exercise. After collection, part of the blood samples will be immediately used for assessment of hematological and lipid profile parameters (complete blood count and lipidogram), albumin, prealbumin, lactate, and coagulation system factors (fibrinogen, D-dimer, plasminogen activator inhibitor-1 (PAI-1), and tissue plasminogen activator). The other part of the sample will be centrifuged to obtain plasma that will be stored at -80°C and used in the future for measurement of insulin-like growth factor-1 (IGF-1), IL-1β, and IL-6. Additionally, the myokines irisin and lubricin will be evaluated. IL-6 was chosen for its role in cytokine regulation and its sensitivity to both surgical trauma and exercise [14,20]. IGF-1 reflects anabolic and regenerative processes, supporting muscle recovery in aging populations [14,21]. Exercise induces the release of myokines such as irisin and lubricin, which may modulate pain and delay osteoarthritis progression via mitochondrial metabolic reprogramming [22], while lactate may indicate inadequate perfusion [23]. Irisin was included due to its association with metabolic modulation and potential chondroprotective effects, especially relevant in osteoarthritis progression and exercise adaptation [22].

Synovial fluid biomarkers

Synovial fluid will be collected immediately before the surgical incision, following sterile field placement and ischemia, using a 20 mL syringe with a 1.2 × 40 mm needle. The sample will be centrifuged at 500 × g for 5 min, and the supernatant will be aliquoted and stored at -80°C until analysis. Cytokine levels (IL-1β, IL-4, IL-12, IL-6, IL-8, IL-10, IL-1β, and TNF-α) will be assessed using a flow cytometry assay (BD™ Cytometric Bead Array (CBA) Human Inflammatory Cytokine Kit). Free DNA levels will be measured using a DNA intercalating probe (Picogreen).

Tissue biomarkers

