Patient satisfaction will be assessed 30 days post-TKA using a validated TKA satisfaction questionnaire [27]. This time point was selected to capture the short-term functional and symptomatic benefits of prehabilitation when effects on recovery are most tangible. Four primary questions, rated on a five-point Likert scale, will evaluate pain relief, functional improvement, and overall satisfaction. Scores ranged from 0 (very dissatisfied) to 100 (very satisfied), with the total score calculated as the mean of all responses. The total satisfaction score will be obtained by summing the individual scores of the four satisfaction questions and dividing by four. If any individual component is missing, the total score will not be calculated.

Sample size

The sample size was estimated using repeated measures analysis of variance with four time points (nine weeks pre-TKA, one day pre-TKA, three days post-TKA, and 30 days post-TKA) and two groups (experimental and control). Assuming a moderate effect size (f = 0.25), α = 0.05, and 80% power (β = 0.20), 78 participants were required (G*Power 3.1.9.7, University of Kiel, Germany). This effect size was selected based on evidence from a study in TKA patients with CRP as the primary outcome, which reported a between-group difference of 9.12 mg/L and a pooled standard deviation of 10.95, corresponding to a Cohen’s d of 0.83 (f ≈ 0.29), and statistical power of 88% with 61 participants. Therefore, f = 0.25 was adopted as a conservative and evidence-based estimate for the current trial [28]. Accounting for a 10% potential attrition rate, the final target sample size was 86 participants.

Blinding

This study follows a single-blind design, in which only the data analyst remains blinded to group allocation. Due to the nature of the intervention (an exercise program), blinding participants or intervention providers was not feasible, as doing so would compromise adherence, safety, and protocol fidelity. Consequently, participants, data collectors, and outcome assessors will be aware of group assignments.

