## Results

The significance level was set at p < 0.05, and analyses will be performed using IBM SPSS Statistics 21.0 (IBM®, Armonk, NY, USA). Data normality will be assessed using the Shapiro-Wilk test. Baseline demographic characteristics will be compared between the groups using independent t-tests (normal data), Mann-Whitney U tests (non-normal data), and chi-square or Fisher’s exact tests (categorical variables).

The primary outcome, changes in plasma CRP levels across four time points (nine weeks pre-TKA, one day pre-TKA, three days post-TKA, and 30 days post-TKA), and WOMAC scores across three time points (baseline, one day pre-TKA, and 30 days post-TKA) will be analyzed using two-way repeated-measures ANOVA (group × time interaction), contingent upon assumptions of normality and sphericity. If these assumptions are violated, linear mixed models (LMM) or generalized estimating equations (GEE) will be employed as more robust alternatives, capable of handling missing data and irregular intervals. Post-hoc pairwise comparisons will use the Bonferroni correction to adjust for type I errors. For non-parametric repeated measures, the Friedman test will be used, followed by Dunn-Bonferroni post-hoc tests when applicable.

Secondary outcomes, including synovial fluid and tissue biomarkers, hospital outcomes (length of stay, complications, readmissions), and satisfaction scores at specific time points, will be compared between groups using independent t-tests (normal data) or Mann-Whitney U tests (non-normal data). Correlations between biomarkers, hospital outcomes, WOMAC scores, and satisfaction will be examined using repeated measures correlation (rmcorr) for normal data or generalized linear mixed model (GLMM) for non-normal data. Rmcorr will be applied when assessing the strength and direction of associations between two continuous variables measured repeatedly within individuals. GLMM will be used in cases requiring the modeling of random effects, adjustment for covariates, or handling of non-normal or categorical outcomes, ensuring analytic flexibility across diverse data structures. To account for multiple comparisons in biomarker and exploratory analyses, false discovery rate (FDR) adjustment will be applied where appropriate.

Effect sizes (e.g., partial eta-squared for ANOVA and Cohen’s d for pairwise tests) and 95% confidence intervals will be reported alongside p-values to enhance the clinical interpretability of findings.

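### Repeated measures correlation between blood biomarkers leaves the common surgical time course in, and the rule for outcomes measured once is unclear

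*Protocol article*

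**What the plan says.** All the relevant rules are in the Results section of the protocol article, which holds the statistical methods. The variables to be related are "Correlations between biomarkers, hospital outcomes, WOMAC scores, and satisfaction", and these "will be examined using repeated measures correlation (rmcorr) for normal data or generalized linear mixed model (GLMM) for non-normal data". Two sentences then qualify this. The first: "Rmcorr will be applied when assessing the strength and direction of associations between two continuous variables measured repeatedly within individuals". The second: "GLMM will be used in cases requiring the modeling of random effects, adjustment for covariates, or handling of non-normal or categorical outcomes". No sentence names visit, surgery or arm as a term in the association analysis. FDR adjustment is planned where appropriate.

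The measurement schedule is spread over several sections:

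- **Blood markers** (Primary outcome; Additional blood biomarkers): four draws, "before and after the eight-week prehabilitation program and three and 30 days post-TKA". On the third draw: "The third postoperative day (t5) was selected to capture the peak inflammatory response following surgery".
- **WOMAC**: three moments (multidisciplinary consultation, pre-hospitalization, 30-day follow-up), none at day 3.
- **Satisfaction**: once. "Patient satisfaction will be assessed 30 days post-TKA using a validated TKA satisfaction questionnaire".
- **Length of stay, readmission, complications**: one value per patient, covering up to 30 days.
- **Synovial fluid and tissue markers**: one sample per patient, taken at the operation.

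**The concern.** Rmcorr estimates one common within-patient slope after centring each patient on his or her own mean. It does not centre on visit. One of the four blood draws is placed on purpose at the surgical CRP peak, and IL-6 was picked partly because it reacts to surgery: "IL-6 was chosen for its role in cytokine regulation and its sensitivity to both surgical trauma and exercise". If two markers both move after the operation, their visit means move together, and rmcorr counts that as association. The result shows that everyone had surgery. It would be read as saying that patients with a larger rise in one marker have a larger rise in the other. FDR control does not help, because each p-value tests a null that includes the common time course.

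The second problem is the switching rule. Normality decides between rmcorr and GLMM, yet the list includes variables with one value per patient. For these the deciding property is whether the variable is repeated, not its distribution.

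**Working it through.** **Inputs from the document.** N = 78 (Sample size, before attrition); four blood visits; three WOMAC visits; significance level 0.05, taken as two-sided. The plan states no figure for the correlation analysis, so there is nothing to reproduce.

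**Assumptions.** The size of the surgical shift is not given. I take each marker's mean profile over the four draws as (0, 0, h, 0.3h), with h in within-patient SD units and varied from 0.25 to 4. The true within-patient association is zero unless stated.

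**Expected rmcorr for two blood markers.** Per patient, the visit profile contributes a sum of squares about its own mean of h²(1 + 0.09) − 4(0.325h)² = 1.09h² − 0.4225h² = 0.6675h². Within-patient noise contributes (4 − 1) × 1 = 3. With no true association only the profile enters the cross-product, so

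r ≈ 0.6675h² / (0.6675h² + 3).

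The error df are 78 × 3 − 1 = 233, so |r| must exceed about 1.97/√(233 + 1.97²) = 0.128 for p < 0.05. The rejection rates below are simulated.

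| h (within-patient SD) | expected r | trials with p < 0.05 |
|---|---|---|
| 0.25 | 0.0417/3.0417 = 0.01 | about 6% |
| 0.5 | 0.1669/3.1669 = 0.05 | about 13% |
| 1 | 0.6675/3.6675 = 0.18 | about 80% |
| 2 | 2.67/5.67 = 0.47 | 100% |
| 3 | 6.0075/9.0075 = 0.67 | 100% |
| 4 | 10.68/13.68 = 0.78 | 100% |

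With visit means also removed (df = 77 × 3 − 1 = 230), mean r is 0.00 and rejection is about 5% throughout.

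**Sensitivity to the assumed shape.** With nothing left at day 30, the profile term is h²(1 − 1/4) = 0.75h², so r at h = 1 is 0.75/3.75 = 0.20. With 60% left it is h²(1.36 − 1.6²/4) = 0.72h², so r = 0.72/3.72 = 0.19. The 30% figure hardly matters; the height does. The heights need not be equal either. With h = 2 for one marker and 0.5 for the other, r = 0.6675 × 2 × 0.5 / √(5.67 × 3.1669) = 0.6675/4.24 = 0.16.

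**Sign reversal.** With a true within-patient correlation of −0.40 and h = 2 for both, r ≈ (2.67 − 0.40 × 3)/5.67 = 1.47/5.67 = +0.26. The visit-adjusted version returns −0.40.

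**Marker-WOMAC pairs.** Only three visits are shared. Take profiles (0, 0, a) for the marker and (0, 0, b) for WOMAC. The cross-product is (2/3)ab and the noise term is 2, so

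r ≈ (2/3)ab / √[((2/3)a² + 2)((2/3)b² + 2)].

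If the marker is back at baseline, a = 0 and r = 0 whatever WOMAC does; rejection is about 5%. With a = 0.5 and b = −1, r = −0.333/√(2.167 × 2.667) = −0.14, significant in about 42% of trials.

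**Outcomes measured once.** The within-patient sum of squares is 0, so rmcorr is 0/0. With one observation per patient the df would be 78 × 0 − 1 = −1.

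**The case against.** Several points count against a broad version of this concern, and most of them stand.

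- *The planned links between biomarkers and recovery are spurious.* A reader might infer this, but the document does not support it. WOMAC is the only repeated recovery measure and has no day-3 value, so the surgical peak never enters those pairs. Only a shift persisting at day 30 can bias them.
- *Rmcorr will be run on length of stay or satisfaction and be undefined.* This too is tempting. The sentence after the normality rule limits rmcorr to pairs measured repeatedly, so the plan does not clearly intend it. What is left is an inconsistency between adjacent sentences.
- *Most outcomes measured once already have a route.* Categorical and non-normal outcomes go to GLMM. This narrows the gap to a continuous, normally distributed variable measured once, but does not close it.
- *GLMM allows covariates, so visit can be added, and covariate choice is commonly left to a fuller plan.* True for the GLMM branch. Visit is not named there, though, and a GLMM with only a patient effect keeps the shared time course. The rmcorr branch is a specific estimator that has no visit term as named.
- *The size is assumed.* Correct. A shared day-3 peak is documented only for CRP. The Discussion says IL-6 rises earlier, and no day-3 peak is stated for D-dimer or fibrinogen. The bias needs only that both markers' visit means shift together, but how much they do so is unknown, and at 0.25 SD it is negligible.
- *The correlations are not among the stated objectives.* Also correct, and it limits the severity. They will still be interpreted, since the Introduction gives the unclear relation between the intervention, biomarker levels and hospital outcomes as a motivation.

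**Conclusion.** The concern holds in a limited form. For pairs of repeatedly measured blood markers, plain rmcorr mixes the common visit profile with the patient-level association. False positives run from about 6% at an assumed shared peak of 0.25 within-patient SD to 80% at 1 SD and 100% at 2 SD or more, and a true negative association can appear positive. These figures rest on assumed heights, equal profiles in the two markers and 78 complete patients. Marker-WOMAC pairs are affected only if the marker remains shifted at day 30. For outcomes measured once, the two sentences on rmcorr conflict and a normally distributed one has no clear method. The point is minor: it concerns secondary association analyses and leaves the primary group comparison and the sample size untouched.

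**What to change.** 1. For pairs measured repeatedly, estimate the association with visit and arm in the model: either rmcorr with visit added as a factor, or a linear mixed model with patient, visit and arm. Patient centring already absorbs a constant arm difference, so in the rmcorr version arm matters through visit means that differ by arm.
2. Name visit and arm in the GLMM branch as well.
3. Choose the method by whether the variable is repeated, not by normality, and reconcile the two sentences accordingly.
4. For length of stay, complications, readmission, satisfaction, and synovial and tissue markers, use a rank correlation or a regression on the biomarker at one named visit. Adjust the regression for arm and, where the marker is a post-baseline blood value, for its baseline value.

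The cost is analysis wording only; no new data and no change in sample size. The downside is that the reported correlations will be smaller.

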Adherence to the prehabilitation program will be assessed by calculating the percentage of completed sets compared to the total prescribed sets. This information will be recorded in the training diary and reported by the patient or a family member. The number and classification of adverse events occurring during the home-based training period will be recorded separately from hospital outcomes.

Adherence will be operationally defined as the completion of ≥75% of prescribed sessions, based on adherence rates commonly reported in the literature. A recent systematic review by Adebero et al. [7] found that most prehabilitation trials achieved adherence rates of 74% or higher, supporting the use of this threshold. This cutoff will be used to determine eligibility for per-protocol analyses evaluating intervention efficacy, while all randomized participants will be retained in the dose-response analysis, regardless of adherence level.

Hospital outcomes

Hospital outcomes will include the length of hospital stay (in days), hospital readmission rate, and number and classification of complications occurring within 30 days post-surgery. These indicators were selected to complement the biological and functional recovery metrics, offering system-level proxies for early recovery quality. Specifically, reduced length of stay may reflect improved physiological readiness for discharge, while lower readmission and complication rates may signal enhanced resilience and postoperative recovery. These data will be retrieved from patients’ medical records, which will be accessed using the registration number recorded during patient enrollment. Surgical complications will be defined as any adverse events based on the Clavien-Dindo classification [26].

Satisfaction level

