Missing data will be addressed using linear regression models to examine the dose-response relationship, including participants who did not reach the ≥75% adherence threshold as well as those who withdrew from the intervention due to comorbidities or frailty. These individuals will be retained in the analysis to reflect real-world variability.

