We recognized potential challenges related to adherence and digital proficiency within our target age population (50-75 years). Cognitive impairments may also influence participation. However, we anticipate that video-based interactions will enhance motivation, accountability, and social support by closely replicating in-person coaching. Evidence suggests that frequent participant contact via telephone, Internet, or personal visits improves adherence to home-based exercise programs among older adults [33]. Telecommunication difficulties between participants and researchers are expected; however, to mitigate these issues, we will provide clear instructions for video call setup and allocate sufficient time to address technical challenges within our study schedule. We anticipate that technical barriers will be most prominent at the beginning of the program and diminish as participants become more accustomed to the process. Notably, a recent Brazilian study demonstrated that WhatsApp-based audio and visual messaging was effective in delivering a six-week psychosocial intervention to older adults, even without direct support from health professionals [34].

Another methodological limitation is the single-blind design, which may introduce performance and detection bias, particularly in subjective outcomes. To mitigate these biases, all outcome assessments will follow standardized protocols and be conducted by the same team of trained evaluators across both groups. Furthermore, participants in both arms will receive uniform instructions regarding their routine daily activities between baseline and surgery, minimizing behavioral discrepancies apart from the intervention itself. While self-reported outcomes are inherently prone to bias, they are measured using validated instruments with low response bias. In addition, we will perform sensitivity analyses to explore the robustness of results by accounting for potential confounders such as adherence, engagement levels, and expectancy effects. Importantly, the trial also includes objective outcomes, such as biomarkers, length of stay, complications, and anthropometric data, which enhance the overall internal validity of the findings despite the inherent limitations of a non-blinded behavioral intervention.

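### The stated missing-data method is an adherence regression that does not handle missing CRP, and the mixed model that could do so is used only if a normality or sphericity check fails

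*Protocol article*

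**What the plan says.** All references are to the protocol article.

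- **Results, missing data.** "Missing data will be addressed using linear regression models to examine the dose-response relationship". The sentence goes on to cover patients below the 75% adherence threshold and those who stopped the programme because of comorbidity or frailty, and adds: "These individuals will be retained in the analysis to reflect real-world variability".
- **Results, primary analysis.** CRP at four time points "will be analyzed using two-way repeated-measures ANOVA (group × time interaction), contingent upon assumptions of normality and sphericity". If those assumptions fail, linear mixed models or GEE "will be employed as more robust alternatives, capable of handling missing data and irregular intervals". A Friedman test is also offered for non-parametric repeated measures.
- **Prehabilitation adherence.** On the 75% threshold: "This cutoff will be used to determine eligibility for per-protocol analyses evaluating intervention efficacy". In contrast, "all randomized participants will be retained in the dose-response analysis, regardless of adherence level".
- **Enrollment.** Patients who do not attend telerehabilitation sessions or do not answer WhatsApp contact are excluded. Those with unexpected complications, infections among them, leave both the programme and the study.
- **Discussion, Strengths and limitations.** Sensitivity analyses are planned "accounting for potential confounders such as adherence, engagement levels, and expectancy effects".

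**The concern.** The sentence that is meant to settle missing data answers a different question. Low adherence and stopping the exercises are departures from the intervention. A missing CRP is an absent outcome. A patient without the outcome cannot enter a regression of that outcome on adherence, so the promise of retention cannot be kept by this method.

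The tool that does use incomplete series is already named, but its trigger is distributional shape. If the checks pass, the ANOVA is run and incomplete patients are likely to be lost. If they fail, the same patients may be kept. The analysed set for the primary outcome would then turn on a test unrelated to missingness.

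This matters because losses here need not be random. Only the experimental arm has telerehabilitation sessions to miss, and infection, a reason for leaving the study, is named under Primary outcome as something that raises CRP.

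Adherence is also treated as a confounder, although it arises after randomisation and to a programme that only one arm receives.

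**Working it through.** **1. What each stated method does with a patient who lacks one CRP value**

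- Dose-response regression: needs the outcome, so the patient drops out. Nothing is imputed.
- Classical two-way repeated-measures ANOVA: needs all four values, so the patient drops out. The Friedman test likewise needs complete blocks.
- Likelihood-based mixed model: uses the values that exist. It is reached only through a failed normality or sphericity check.
- Full retention of randomised patients is promised only for the dose-response analysis.

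**2. The plan's own sample size**

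Inputs (Sample size): f = 0.25, alpha = 0.05, power 80%, two groups, m = 4 time points, N = 78, raised to 86 for 10% attrition. The within-patient correlation rho is not given, so 78 cannot be reproduced from the stated inputs alone.

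- Between-group test: lambda = N f² m / (1 + (m − 1) rho), df 1 and N − 2. At rho = 0.5, power at N = 78 is 0.787 and 82 are needed. At rho = 0.47, power at 78 is 0.802. So 78 fits a between-group test with rho of about 0.46 to 0.47.
- Group × time test: lambda = N f² m / (1 − rho), df 3 and 3(N − 2). At rho = 0.5, 24 are needed.
- Attrition: 78 × 1.10 = 85.8, giving 86 (78 / 0.9 = 86.7 would give 87).

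**3. Complete cases (illustration)**

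Baseline is complete before randomisation, so three later samples can be missing. Assume each is missing independently with probability q. The article gives no such rate. Complete cases = 86 (1 − q)³:

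- q = 3%: 86 × 0.913 = 78.5
- q = 5%: 86 × 0.857 = 73.7
- q = 10%: 86 × 0.729 = 62.7

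If instead the same 10% of patients miss every later sample, 86 × 0.9 = 77.4 remain.

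**4. Power with 63 complete cases**

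Group × time at f = 0.25, df 3 and 183, under sphericity:

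- rho = 0: lambda = 63 × 0.0625 × 4 / 1 = 15.75, power 0.925
- rho = 0.2: lambda = 15.75 / 0.8 = 19.69, power 0.97
- rho = 0.5: lambda = 15.75 / 0.5 = 31.5, power 0.999

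For a between-group test at rho = 0.5, power at q = 3%, 5% and 10% is 0.79, 0.76 and 0.69, against 0.83 with all 86. That test is not the one Results names.

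**5. Adherence as a covariate**

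Suppose Y = b0 + b1·group + b2·adherence, with controls coded 0. The arm difference at adherence a is b1 + b2·a, so b1 is the contrast at zero adherence. If benefit is proportional to the exercise done, b1 = 0 however large the benefit.

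An illustrative simulation used 86 patients, 4,000 runs and a single CRP comparison with no true effect. Frailty was assumed to correlate 0.5 with CRP and to drive adherence and missingness in the experimental arm. Rejection rates at the 5% level were:

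- randomised comparison, full data: 5%
- complete cases: 6%
- dose-response within the experimental arm: 65%
- group effect adjusted for adherence: 56%

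These rates follow from the assumptions and show direction only.

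**The case against.** The article does name methods it describes as "capable of handling missing data and irregular intervals". CRP with a peak on day 3 may well fail normality or sphericity, which would bring the mixed model in anyway. Listwise deletion is nowhere stated; it is a property of the classical ANOVA. The day-3 sample is taken in hospital and is less likely to be missed, and dropout tends to remove the same person from several samples, so the independent-missingness counts may be too pessimistic. The confounder remark sits among the limitations, concerns sensitivity analyses only and specifies no model.

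All of this stands, and it narrows the point. It does not rescue the missing-data sentence, which asserts a method that cannot do what is claimed. Nor does it repair the trigger: a mixed model that is probable is not one that is planned, and a failed check could lead to GEE or Friedman instead.

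A reader might go further and infer that more than about 3% missing per visit breaks the stated power. The documents do not support that. The 78 is undercut just above 3% per visit under independent missingness, but the named group × time test keeps power above 0.9 at 63 complete cases. The shortfall below 80% appears only for a between-group test that Results does not name as primary.

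**Conclusion.** The concern holds in limited form. The stated missing-data method is not one, and use of incomplete CRP series is tied to the wrong condition. The consequence is possible selection bias and some loss of precision in the primary comparison. Its size cannot be fixed from the article, which gives no per-sample missing rate and no within-patient correlation. Bias in the primary comparison is plausible from the exclusion rules but not demonstrated: in the illustration, complete-case analysis rejected in 6% of runs against a nominal 5%.

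Calling adherence and engagement confounders is wrong for a randomised comparison, and adjusting for adherence can bias the group effect. It would be an over-reading to say that the plan adjusts its primary analysis this way. The contrast-at-zero-adherence result depends on a linear term with controls coded 0, which the article does not specify.

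The Enrollment rules that exclude patients or withdraw them from the study also conflict with the retention promised under Prehabilitation adherence and in Results.

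**What to change.** 1. Replace the missing-data sentence in Results. State that CRP is analysed primarily with a likelihood-based mixed model, whatever the assumption checks show, including every randomised patient in the assigned group with any available CRP data, and that this is valid under missing at random.
2. Label the dose-response regression exploratory and say that it is not a missing-data method.
3. Remove adherence and engagement as covariates in arm comparisons, and stop calling adherence a confounder.
4. Reconcile the exclusion and withdrawal wording under Enrollment with the retention stated under Prehabilitation adherence and in Results. A mixed model cannot use CRP values that were never collected after a patient left the study.

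The cost is a change of analysis wording and slightly more analysis work. The mixed model is already named in the article, and the sample size need not change on account of this point.
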